## Abstract

Chronic diseases typically require long-term management through healthy lifestyle practices and pharmacological intervention. Although efficacious treatments exist, disease control is often sub-optimal leading to chronic disease-related sequela. Poor disease control can partially be explained by the ‘one size fits all’ pharmacological approach. Precision medicine aims to tailor treatments to the individual. CURATE.AI is a dosing optimisation platform that considers individual factors to improve the precision of drug therapies. CURATE.AI has been validated in other therapeutic areas, such as cancer, but has yet to be applied in chronic disease care. We will evaluate the CURATE.AI system through a single-arm feasibility study (*n* = 20 hypertensives and *n* = 20 type II diabetics). Dosing decisions will be based on CURATE.AI recommendations. We will prospectively collect clinical and qualitative data and report on the clinical effect, implementation challenges, and acceptability of using CURATE.AI. In addition, we will explore how to enhance the algorithm further using retrospective patient data. For example, the inclusion of other variables, the simultaneous optimisation of multiple drugs, and the incorporation of other artificial intelligence algorithms. Overall, this project aims to understand the feasibility of using CURATE.AI in clinical practice. Barriers and enablers to CURATE.AI will be identified to inform the system’s future development.

## 1. Introduction

Chronic disease management typically requires long-term adherence to medication and lifestyle modifications [1]. While substantial efforts have gone into finding effective drug therapies and developing self-management support interventions, many chronic disease patients remain sub-optimally controlled [2,3]. One of the most significant limitations of today’s treatment regimens is the ‘one size fits all’ approach to disease management. For instance, drug dosing regimens follow standardised guidelines derived from population-based studies. These studies often do not include the diverse profile of patients clinicians face daily and thus the derived clinical guidelines are not fully representative [4]. While clinicians may use some discretion when treating patients, drug dosing decisions continue to be based on a limited number of variables, such as age, major organ function and severity of the disease. However, treatment success is dependent on a much broader spectrum of factors; genetics, environmental conditions, patient characteristics, and pharmacology can all influence an individual’s response to therapy [5,6,7]. Taking account of a greater degree of individual-level factors, tailored therapies or ‘precision medicine’ has emerged as an approach to improve disease management. 

Although precision medicine is generally regarded as a modern concept, the first known example can be traced back to blood group identification in 1901, leading to successful blood transfusion practices [8]. More recently, many advancements in the precision medicine field have been attributed to the human genome project. Mapping the human genome has substantially advanced knowledge on the role of genes in health and disease [9]. By accounting for individual variability, precision medicine can improve treatment efficacy and reduce unnecessary tests or adverse reactions [10]. However, there is still a pressing need to develop approaches and technologies that consider the spectrum of factors unique to individuals. Artificial intelligence (AI) may be one route to utilise a greater breadth and complexity of data to optimise treatment decisions. 

Amongst the many unique features of AI, a unifying concept revolves around the fact that AI can reconcile large amounts of data into actionable care management strategies. Applications in digital pathology and robotic surgery have been widely publicised [11]. In chronic disease, examples of AI applications include digital health programmes [11], conversational agents (e.g., chatbots) [12], games to promote physical activity [13], clinical decision support systems [14], wearables (i.e., to track disease management, physical activity, or disease exacerbations) [15], diagnostics, and prediction of chronic disease complications [16]. A novel dosing optimisation system—CURATE.AI—is the latest innovation that has the potential to improve chronic disease care. 

CURATE.AI is an actionable dosing optimisation platform, initially developed to improve the precision of chemotherapy dosing. The algorithm considers the treatment response over time, predicting the dosing needs dynamically to maintain the required levels of efficacy and safety. CURATE.AI has been validated in other disease indications [17,18,19] (e.g., oncology, immunosuppression, and infectious diseases) but has yet to be applied in patients with chronic disease. This study aims to demonstrate the feasibility of using an artificial intelligence-guided system to optimise medication dosing in hypertensive and type II diabetic patients. The study objectives are:To assess the clinical outcomes of patients treated using CURATE.AI technology.To evaluate the staff experiences of implementing and using the CURATE.AI system in clinical practice and identify the facilitators and barriers to its use.To elicit the opinions and experiences of patients receiving CURATE.AI guided care.To optimise the CURATE.AI algorithm through exploratory analysis, including artificial intelligence algorithms.

## 2. Materials and Methods

We will evaluate the CURATE.AI system in clinical practice through a single-arm feasibility study. The evaluation will be guided by modified versions of ‘The Non-adoption, Abandonment, Scale-up, Spread, and Sustainability’ (NASSS) and the Higgins & Madai (2020) frameworks on the development of artificial intelligence systems in healthcare. Quantitative and qualitative data will be collected through: (i) prospective collection and analysis of clinical data and (ii) staff and patient interviews. Exploratory analysis will investigate how best to optimise the algorithm using retrospective patient data.

### 2.1. The CURATE.AI System 

Details of the CURATE.AI algorithm have been published before [17,18,19,20,21]. In brief, CURATE.AI represents the drug input and output relationship by a second-order polynomial equation. The algorithm is calibrated to each patient using three input–output data points, creating a parabola. The parabola determines the drug inputs required to keep a patient within the output range. The parabola is continuously calibrated as further data are entered (Equation (1)). 

In this study, the input refers to the drug dose, and the output corresponds to blood pressure, HbA1c, or blood glucose. The algorithm can optimise multiple drugs simultaneously, although initially, we will only optimise a single principal drug. 

Equation (1) CURATE.AI algorithm.
(1)$$R\left(C,t\right)=F\left(S^{\prime },\;C,\;t\right)-F\left(S^{\prime },\;t\right)=x_{0}+\sum x_{i}c_{i}+\sum y_{ii}c_{i}^{2}+\sum z_{ij}c_{i}c_{j}\;$$

*R* (*C*, *t*) represents the overall treatment response; *F* (*S′*, *C*, *t*) represents a diseased patient under treatment; *F* (*S′*, *t*) represents the diseased patient; *S′* comprises the disease mechanisms; *C* represents the drug type and dose. Finally, *t* shows that every term in the series can vary with time and should be continually re-calibrated with clinical or point-of-care data. With regard to CURATE.AI-driven patient calibration, *x_i_* is the patient response coefficient to drug *i* at concentration *c_i_*, *y_ii_* represents the second-order response to the drug concentration *c_i_*, and *z_ij_* is the patient response coefficient to the interaction of drug *i* and drug *j* at their respective concentrations. To implement CURATE.AI, the values of *x*_0_, *x_i_*, *y_ii_*, and *z_ij_* are clinically/experimentally determined by calibrating phenotypic outputs of a specific patient and the drug dose inputs, leading to a personalised drug–dose combination for a specific patient.

### 2.2. Retrospective Study

CURATE.AI has been previously validated in retrospective and prospective studies [20] but has not been used in chronic disease states. We will conduct a retrospective analysis of patient data for two purposes. Firstly, an optimised dosing schedule will be generated using historical patient data on dose–response relationships. The aim is to demonstrate that a dosing schema can practically be generated and is clinically acceptable. 

Secondly, the dataset will be used to explore different ways of optimising the CURATE.AI algorithm. Examples include the inclusion of other covariates, which may impact the input–output response; the optimisation of multiple drugs simultaneously; whether calibration can be achieved with fewer calibration data points; and the use of different statistical models to forecast output responses, such as linear or polynomial regression or neural network regression.

For the exploratory analyses, outpatient records (hypertensives and type II diabetics) from 1 June 2018 to 30 September 2020 will be retrospectively extracted from Alexandra Hospital and the National University Hospital. Both institutions contribute to the same Electronic Health Record (EHR), which captures the patients’ health journeys across different health care providers. Details of medical histories, inpatient admissions, outpatient clinic visits, diagnostics, and medication prescriptions are captured by the EHR.

Factors associated with treatment response in patients with hypertension and type II diabetes are well reported [22,23,24,25,26]. Where possible we will extract these data. The following variables will be extracted: age, gender, race, marital status, residency status, postal code, diagnoses, subsidy status, visit date, referring institution, procedures or investigations and corresponding results, Charlson comorbidity index, and medication.

### 2.3. Prospective Study

#### 2.3.1. Participants

Forty patients (*n* = 20 hypertensives and *n* = 20 type II diabetics) will be recruited from the outpatient clinic at Alexandra Hospital, Singapore, during their routine clinic visits. The primary physician will identify potentially eligible participants and notify the research team. A research team member will discuss the project with the participant, screen for eligibility, and take consent. If a patient has both type II diabetes and hypertension, the treating physician will decide which study arm the patient should enrol on. Patients may be newly diagnosed or be those with established but poorly controlled disease. The presence of comorbidities and all prescribed medications will be tracked. The eligibility criteria are as follows: 

##### Inclusion Criteria

Adult patients (≥21 years) with clinically diagnosed type II diabetes or hypertension.

Expected to be followed up at Alexandra Hospital in the next six months.

##### Exclusion Criteria

Patients with cognitive impairment.

Patients with active cancer undergoing chemotherapy.

Patients on haemodialysis or peritoneal dialysis (which can cause rapid fluctuation of BP and blood sugar, respectively).

Pregnant patients.

Patients with type II diabetes and hypertension whose medications are changed simultaneously during their first clinic visit.

Patients with controlled HbA1c or blood pressure at baseline.

Serious concomitant disorders that would compromise the safety of the patient or their ability to complete the study. This may include a recent occurrence of stroke or sub-arachnoid haemorrhage in hypertensive patients, which necessitates tighter control, and occurrence of renal failure or lactic acidosis in patients with type II diabetes, which may warrant avoidance or reduction in metformin dose.

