#### 2.3.2. Outcome Measures

We will report on clinical and qualitative outcomes relating to CURATE.AI’s effect, implementation, and acceptability. The following clinical outcomes will be reported:Proportion achieving blood pressure and glycaemic control at four months.Average number of days until blood pressure or glycaemic control is first achieved.Proportion relapsing after disease control is achieved (i.e., high blood pressure).Proportion compliant with clinic follow-up.Proportion compliant with home monitoring of blood pressure or glucose.Number of dropouts.Proportion of dosing decisions recommended by CURATE.AI but not implemented at the physician’s discretion and the magnitude of difference.

The study’s main purpose is to explore the feasibility of the CURATE.AI system in clinical practice and not to establish efficacy or effectiveness. The clinical outcomes are included to show the preliminary effects of the intervention. Qualitative work will seek to understand the practicalities of using the system in clinical practice, identify implementation barriers and enablers that can inform future development of the system, and to advance the processes associated with using CURATE.AI.

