Participants will be followed up monthly for four months. Clinically, blood pressure may be controlled with medication within four to six weeks [33]. For type II diabetes, although traditionally changes in HbA1c are assessed every three months, emergent evidence suggests clinically relevant changes may occur as early as one month [34]. Based on these data, four months was deemed appropriate to observe clinical improvements as well as being a sufficient period to test the system. Clinic visits may be face-to-face or virtual as appropriate. If a dosage change is required at a clinic visit, hypertensive participants will be asked to monitor their ambulatory blood pressure for a single six-hour period at home (once hourly). A six-hour ambulatory blood pressure recording is equivalent to a twenty-four-hour reading [35]. Patients will then continue to monitor blood pressure twice daily, morning and evening, for up to seven days. Following any change of type II diabetic medications, patients will be asked to wear a continuous glucose monitoring device for a minimum of seven days at home (the maximum wear time is fourteen days). Monitoring will commence fifteen days after the dose change is initiated (for either hypertensives or type II diabetics), so a steady state can be reached before assessment. These data will feed back into the CURATE.AI system, and further recommendations on dose adjustment will be generated if required. The treating physician will regularly review remote monitoring data for safety. If the patient’s medication is changed entirely, recalibration with CURATE.AI is required. At the last clinic visit, patients will be interviewed using a semi-structured survey on their experiences with the CURATE.AI system. 

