#### 2.3.5. Data Analysis

All analyses will be conducted using STATA version 15.0 (STATA Corp, College Station, TX, USA). As appropriate, summary statistics will be presented as means with standard deviation, medians with interquartile ranges, and percentages. Clinical outcomes will be analysed separately for the hypertensive and type II diabetic groups. Blood pressure control is defined as a home or ambulatory blood pressure of less than 135/85 mmHg or office readings below 140/90 mmHg, unless otherwise defined by the treating physician [39]. Glycaemic control is defined as HbA1c < 7% [40] or glycaemic variability ≤ 36% or time in normal range (4.0 to 10.0 mmol/L) > 70% [41]. The proportion of patients achieving blood pressure control and glycemic control will be calculated by comparing the baseline reading to the four-month follow-up. A within-subject analysis of hypertensive and glycemic control will be conducted using the Chi^2^ or McNemar’s test, if cell counts are small (<5). The proportion achieving clinically relevant reductions in systolic and diastolic blood pressures by the four-month follow-up will be determined. The number of days until blood pressure or glycaemic control is first achieved will be calculated. The occurrence of relapse after control has been achieved (i.e., high blood pressure) will also be determined. 

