**Other data captured:**					
Demographics	X				
Weight, BMI, hip-waist ratio	X	X	X	X	X
Medical history (morbidities, medication)	X				
Renal function	X				X
Liver function	X				X
Details of physical activity (16 items)	X				X
Details of diet (26 items)	X				X
Medication adherence (9 items)	X				X
Change in medications	X	X	X	X	X
Disagreements between CURATE.AI and physician	X	X	X	X	X
Patient survey					X

^a^ Home-monitoring may be scheduled 15 days after dose change, if indicated.

**Table 2 ijerph-19-08979-t002:** Modified NASSS and AI framework domains and associated data sources [36,37].

NASSS Domain	Data Sources
1A/1B: What is the nature of the condition?/What are the relevant sociocultural factors and comorbidities?	Patient profiles and patient interviews
2A: What are the key features of the technology?	The algorithm and desired features identified in staff interviews
2B: What kind of knowledge does the technology bring into play?	Application of algorithm in chronic disease care, and staff and patient interviews
2C: What knowledge and support are required to use the technology?	Patient and staff interviews
3B: What is the technology’s desirability, efficacy, safety, and cost effectiveness?	Study outcomes, and patient and staff interviews
4A: What changes in staff roles, practices, and identities are implied?	Staff interviews
**AI Framework Domain**	**Data Sources**
Data form: Data access, the structure of data, appropriateness of data, data plan	Evaluation of data collection from medical record data, clinic assessments, and home-monitoring
Model development form: Determine the best algorithm type, scalability of the algorithm	Algorithm development through retrospective analysis of medical record data
Model development build: Pilot test performance of the algorithm	Study outcomes and staff interviews

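### Diabetic patients are screened for control on HbA1c alone, but may count as controlled at four months on sensor measures that are not scheduled at baseline

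*Protocol article*

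**What the plan says.** The first clinical outcome in section 2.3.2 is "Proportion achieving blood pressure and glycaemic control at four months". Four statements bear on it in the diabetic group.

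- **Entry (Exclusion Criteria):** the plan excludes "Patients with controlled HbA1c or blood pressure at baseline". Neither sensor measure is named.
- **Definition of control (2.3.5):** glycaemic control is "HbA1c < 7% [40] or glycaemic variability ≤ 36% or time in normal range (4.0 to 10.0 mmol/L) > 70" per cent. The three criteria are joined by *or*, so any one is enough.
- **Comparison (2.3.5):** the proportion "will be calculated by comparing the baseline reading to the four-month follow-up". The plan adds: "A within-subject analysis of hypertensive and glycemic control will be conducted using the Chi^2^ or McNemar’s test". Significance is set at p < 0.05.
- **Sensor timing (2.3.3 and Table 1):** "Following any change of type II diabetic medications, patients will be asked to wear a continuous glucose monitoring device for a minimum of seven days", starting fifteen days after the change. The Table 1 footnote reads "Home-monitoring may be scheduled 15 days after dose change, if indicated". For glycaemia at baseline and every later visit, Table 1 lists HbA1c or blood glucose; it has no sensor row.

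**The concern.** One measure decides who is uncontrolled at the start, and up to three decide who is controlled later. The two added routes are not scheduled for measurement at baseline, so the comparison cannot separate a patient who came under control from one who met a sensor criterion all along.

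The routes are also unequal across patients. Someone whose medication is not changed has no scheduled sensor recording and can qualify only on HbA1c.

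At stake is the first-listed clinical outcome, which is meant to show preliminary effects and to inform a later efficacy evaluation. Days to first control has the same weakness, since the first sensor recording may register control that was already present.

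**Working it through.** The article gives no expected control rate and no power calculation, so there is no figure of the plan's own to reproduce. The check first compares the definitions and then illustrates the size.

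**1. Definitions side by side (diabetic group)**

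| Point in time | What can classify a patient as controlled |
|---|---|
| Entry | HbA1c |
| Baseline, as scheduled in Table 1 | HbA1c or a blood glucose value; no sensor reading |
| Four months | HbA1c < 7%, or variability ≤ 36%, or time in range > 70% |

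With sensor wear starting 15 days after a change and lasting at least 7 days, a minimum recording is complete no earlier than day 15 + 7 = 22 after that change. Nothing schedules one before the first study dose change.

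**2. Can a patient enter already meeting the endpoint?**

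Yes. HbA1c of 7.4% with time in range above 70% passes the exclusion rule and meets the four-month definition. The variability route also allows it. Taking variability as SD/mean (an assumption), a mean glucose of 11 mmol/L with SD 3 gives 3/11 = 27.3%, which is within 36%. Under a normal approximation the time between 4 and 10 mmol/L is then Φ((10 − 11)/3) − Φ((4 − 11)/3), about 36%. Glucose that is stable but mostly out of range would count as controlled.

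**3. How many such patients move the test?**

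Inputs: n = 20 diabetics (section 2.3.1) and significance at 0.05 (section 2.3.5), taken as two-sided. Suppose every entrant is coded uncontrolled at baseline, because HbA1c is what screened them. All discordant pairs then run one way. The baseline-controlled cells are empty, so the plan's own small-cell rule points to McNemar's test. The exact two-sided p-value with b discordant pairs is 2 × 0.5^b:

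- b = 5: 2 × 0.5^5 = 0.0625
- b = 6: 2 × 0.5^6 = 0.031

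Six of 20 are enough.

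**4. Chance of reaching six with no treatment effect**

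Let q be the share of entrants who already meet a sensor criterion and still meet it at four months. The documents do not give q. The expected number is 20q, and the chance of p < 0.05 from these patients alone is P(X ≥ 6) with X ~ Binomial(n, q). The middle columns assume that all 20 have a four-month recording. The last assumes that only 16 do.

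| Assumed q | Expected of 20 | P(X ≥ 6), n = 20 | P(X ≥ 6), n = 16 |
|---|---|---|---|
| 0.1 | 2 | 0.01 | 0.003 |
| 0.2 | 4 | 0.20 | 0.08 |
| 0.3 | 6 | 0.58 | 0.34 |
| 0.4 | 8 | 0.87 | 0.67 |

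The result depends strongly on q and on how many patients have a recording near four months.

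**The case against.** **This is a feasibility study.** Section 2.3.2 disclaims efficacy, the limitations section says there is no control group, and no decision rule rests on this proportion. That stands and limits the weight of the point. It does not remove it, because the proportion is still reported as a preliminary effect and tested at 0.05.

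**Some sensor data may exist before baseline.** Baseline follows three calibration points, which may need extra visits, and a sensor is worn after any change of diabetic medication. The Table 1 footnote is also attached to the baseline column. A reader might infer that sensor measures are never available at baseline; the documents do not support that. They support only that no baseline reading is scheduled for all patients, and that none is used for eligibility.

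**Baseline scoring is inferred.** Section 2.3.5 gives one definition and does not say that HbA1c alone scores baseline. For a patient without a sensor reading, however, the sensor criteria cannot be scored there.

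**Upward change is built in anyway.** Excluding controlled patients leaves regression to the mean under any criterion, HbA1c included. This stands: matching the criteria removes the patients who already qualified, not the whole artefact.

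**The loose variability criterion is a separate matter.** It would persist even with a baseline sensor. It should therefore not be used to size the mismatch between entry and endpoint.

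**Conclusion.** The mismatch holds on the article's own wording. A diabetic patient can enter with a sensor criterion already met and be counted as having achieved control without changing, while patients with no sensor recording have fewer ways to qualify. The bias runs towards apparent improvement in the four-month proportion and its within-subject test, and it reaches days to first control.

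Its size is not known from the documents. The probabilities of about 0.20 and 0.58 rest on an assumed 20% or 30% of entrants already qualifying, a four-month recording for all 20, all entrants coded uncontrolled at baseline, and an exact two-sided McNemar test. They fall if fewer patients have a recording.

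A reader might also infer that the bias grows with the number of drug changes. The documents do not show this for a four-month proportion: what matters is whether a recording near month four exists, not how many changes came before it. The point is a correction to make before analysis. It does not undermine the feasibility aims.

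**What to change.** - In section 2.3.5, score the diabetic baseline-to-four-month control comparison on HbA1c < 7% only, the measure used at entry.
- In Table 1, require HbA1c itself at baseline and Visit 4. The present entry lets a blood glucose value stand in for it.
- Report time in range and variability separately, as post-baseline descriptions with the number of patients recorded, and not as control achieved. Treat days to first control in the same way.
- State that, because controlled patients are excluded at entry, some apparent improvement from regression to the mean remains even on HbA1c alone.

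The cost is that HbA1c is fixed as the measure at two existing visits, the sensor results move to a supporting table, and the reported proportion controlled will be smaller. No extra visit or device is needed.
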